### Stastical analysis

#### Sample size and accrual

The primary endpoint will be progression of disease at 6 months. Historical data on this patient population indicate that >80% would show progression, within a 6-month period without treatment, and thus this is the progression rate we expect in subjects in the control/observation arm [37–39]. We hypothesize that SABR will reduce progression at 6 months by 50% [40]. A sample size using a 2:1 randomization scheme of 36 in the SABR arm and 18 patients in the control group will provide 85% power to detect a decrease in relapse rate from 80% to 40% with a type I error = 0.05 using one-sided Fisher’s exact test. Thus, we will accrue a total of 54 patients. Patients withdrawing within one month of enrollment or prior to day 1 of SABR or observation will be replaced.

#### Data analysis

##### 2.4.2.1.Analysis of primary objective

A minimization approach [35] will be applied to ensure balanced assignment to each treatment arm by: 1) Initial treatment with surgery vs. radiation therapy; 2) Prior hormonal therapy vs. no prior hormonal therapy; and 3) PSADT <6 mos vs. 6-14.9 mos. Baseline PSA level is defined as that measured Day 1 following randomization.The primary clinical outcome will be the proportion of patients who have progressed after 6 months from randomization. For each arm, we will calculate the proportion of patients who have progressed and extract 95% confidence intervals. If a patient has withdrawn from the study before 6 months, they will be considered to have progressed.Progression will be a composite endpoint defined from the Prostate Cancer Working Group 2 (PCWG2) criteria for mCRPC [38] and our previous trials in a population of men with biochemical failure without metastases [37–39]. Progression will be defined as either: 1) a ≥ 25% increase in PSA from nadir (and by ≥ 2 ng/mL), requiring confirmation ≥ 4 weeks later (PCWG2 criteria); and/or, 2) clinical/radiographic-progression defined as symptomatic progression (worsening disease-related symptoms or new cancer-related complications), or radiologic progression (on CT scan: ≥ 20% enlargement in sum diameter of soft-tissue target lesions [RECIST 1.1 criteria]; on bone scan: ≥ 1 new bone lesions), initiation of ADT or death due to any cause, whichever occurs first. Death is considered a severe adverse event here.We will compare the proportion of patients who have progressed in the observation and SABR arms using Fisher’s exact test. The analysis population includes all randomized subjects based on intention-to-treat.

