### Evaluation of randomization and blinding

This study will employ a randomized phase II design to determine the appropriateness of a subsequent phase III trial based on comparison of rate of progression at 6 months. An interactive web response system (IWRS) will be utilized to obtain the patient’s randomization assignment. Randomization will occur in a 2:1 fashion for SABR and observation arms, respectively. A minimization approach [35] will be applied to ensure balanced assignment to each treatment arm by: 1) Initial treatment with surgery vs. radiation therapy; 2) Prior hormonal therapy vs. no prior hormonal therapy; and 3) PSADT <6 mos vs. 6-14.9 mos. The on-study date for protocol entry will be the day that the study subject is randomized. Patients will be re-evaluated for radiographic response 6 months after randomization. Trial radiologists evaluating for treatment responses will be blinded to the treatment group and treatment specifics. The trial radiologists and the principal investigator will be unblinded only if a patient progresses at any time during the study.

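### Replacement, withdrawal-as-progression and all-randomised ITT conflict for patients who leave early, and scoring every exit as an event exposes the primary test to arm-dependent withdrawal in either direction

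*Protocol article*

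**What the plan says.** Four statements in the protocol article bear on a patient who leaves early.

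- Evaluation of randomization and blinding: "The on-study date for protocol entry will be the day that the study subject is randomized".
- Sample size and accrual: "Patients withdrawing within one month of enrollment or prior to day 1 of SABR or observation will be replaced". Total accrual is 54, with 36 on SABR and 18 on observation.
- Section 2.4.2.1, Analysis of primary objective (the abstract has the same rule): "If a patient has withdrawn from the study before 6 months, they will be considered to have progressed".
- Section 2.4.2.1 again: "The analysis population includes all randomized subjects based on intention-to-treat".

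The design claims 85% power for 80% versus 40% progression at 6 months, "with a type I error = 0.05 using one-sided" Fisher's exact test. The abstract calls the trial non-blinded. The radiologists who read the response images are blinded. No withdrawal rate is given for either arm.

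**The concern.** A man who leaves in week three has already been randomised. One rule has him replaced, another counts him as progressed, and a third places him in the analysis population. The article does not say whether a replaced patient stays in the analysis. Two analysts could therefore build different denominators from the same data and both claim to follow the plan.

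The scoring rule raises a second issue. Patients know their arm, and leaving the study is their own act. Blinded image reading protects the radiological component but not an event created by leaving. If withdrawal differs by arm, part of the observed difference in progression is a difference in withdrawal.

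The primary comparison is meant to decide whether a phase III trial is appropriate, and it rests on 18 controls. Two or three patients can matter.

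**Working it through.** **Inputs from the article.** Observation n=18, SABR n=36; progression 80% and 40%; one-sided Fisher test at 0.05. The side is stated in the sample-size section; section 2.4.2.1 names the test without repeating it.

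**Assumptions.** Withdrawal rates w are mine, because the article gives none. Withdrawal is taken as independent of true progression.

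**Formulas.** With x1 events of n1 on observation, x2 of n2 on SABR, and m = x1 + x2:

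- p = Σ C(n1,k)·C(n2,m−k) / C(n1+n2,m), summed over k ≥ x1.
- Rejection probability = ΣΣ Bin(x1; n1, p1)·Bin(x2; n2, p2) over all outcomes with p ≤ 0.05.
- Observed rate when withdrawals are scored as progression: p′ = p + (1−p)·w.

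**1. The plan's own figure.** With p1=0.80, p2=0.40, n1=18 and n2=36, power is 0.851. The stated 85% is reproduced.

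**2. The denominator.** Suppose the 54 patients who are not early leavers give 12/18 on observation and 15/36 on SABR.

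| Early leavers kept as progressed | Observation | SABR | One-sided p |
|---|---|---|---|
| None (removed) | 12/18 | 15/36 | 0.074 |
| 2 observation | 14/20 | 15/36 | 0.039 |
| 3 observation | 15/21 | 15/36 | 0.028 |
| 2 SABR, 1 observation | 13/19 | 17/38 | 0.079 |
| 2 SABR | 12/18 | 17/38 | 0.106 |
| 3 SABR | 12/18 | 18/39 | 0.124 |

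The conclusion changes when the leavers are all from observation. It does not change when they split 2:1 like the allocation, or when they are all from SABR.

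**3. Type I error with no true effect, 18 versus 36.** Column heads give withdrawal as observation / SABR.

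| Common true rate | 0 / 0 | 20% / 5% | 30% / 5% | 5% / 20% |
|---|---|---|---|---|
| 80% | 2.1% | 3.6% | 5.2% | 1.1% |
| 50% | 3.0% | 8.6% | 15.5% | 0.8% |
| 40% | 3.0% | 10.3% | 19.7% | 0.6% |

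Example at 50% with 20% / 5%: observation 0.50 + 0.50×0.20 = 0.60; SABR 0.50 + 0.50×0.05 = 0.525. At 80% only the remaining 20% of patients can be reclassified, which is why the inflation is small there. Equal withdrawal of 10% leaves the error at 2.0% (80% rate) and 3.0% (50% rate).

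**4. Power at a true 80% versus 40%.**

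- 10% in both arms: 0.80 + 0.20×0.10 = 0.82 and 0.40 + 0.60×0.10 = 0.46; power 78.3%.
- 20% in both arms: 0.84 and 0.52; power 70.0%.
- 20% observation, 5% SABR: 0.84 and 0.43; power 88.4%.
- 5% observation, 20% SABR: 0.81 and 0.52; power 60.0%.

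**The case against.** **The replacement sentence may be only an accrual rule.** It sits under sample size, does not say that leavers are removed, and section 2.4.2.1 fixes the population as all randomised. This is the natural way to reconcile the text, and the fix adopts it. The article does not say it, however, and replacing a patient is often taken to mean that the newcomer stands in for him. On the accrual reading the analysed number exceeds 54, and each early leaver is an automatic event.

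**A reader might infer that the scoring rule biases the trial towards SABR.** The documents do not support that. It requires more withdrawal from observation than from SABR, and no rate is given. Equal withdrawal dilutes the effect, and excess withdrawal from SABR works against SABR.

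**The larger error rates depend on assumptions outside the plan.** The article states: "Historical data on this patient population indicate that >80% would show progression, within a 6-month period without treatment". Near 80%, even 30% versus 5% withdrawal gives only 5.2%. The 8.6% and higher figures need a true rate well below the planned one. This stands, and those figures must be read as conditional.

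**Some scored exits are genuine events.** Initiation of ADT is itself a progression component, so a man who leaves to start ADT would count anyway. The rule misclassifies only exits without progression by another component.

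**Scoring withdrawal as failure is a recognised choice.** It keeps everyone in the analysis. Kaplan-Meier censoring assumes that leaving is uninformative, and imputation would lean on 18 controls with PSA scheduled at Days 1, 90 and 180. A reader might conclude that the primary rule has to be replaced; that does not follow. Sensitivity analyses may also exist in an analysis plan that is not shown, so their absence from the article is not itself a fault.

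**Conclusion.** The point holds in two parts.

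First, the replacement, scoring and population rules are not reconciled for a patient who leaves within a month of randomisation. This conflict is in the text, and an analysis plan could resolve it only by fixing the meaning of one of these statements. Its effect depends on which arm the leavers come from: two observation leavers move p from 0.074 to 0.039 in the example, while a 2:1 split leaves it at 0.079.

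Second, the scoring rule makes the primary test sensitive to unequal withdrawal in both directions. Under the assumed 20% observation versus 5% SABR, type I error is 3.6% at the planned rate, 8.6% at 50% and 10.3% at 40%. With the imbalance reversed it is about 1% or less.

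The stated power is not an arithmetic error. It holds for 36 and 18 patients with no scored withdrawals, and falls to 78% or 70% with equal withdrawal of 10% or 20%. All the withdrawal figures rest on assumed rates and on withdrawal being independent of true progression.

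**What to change.** - State that replacement affects accrual only, and that every randomised patient, including one who is replaced, is analysed in the assigned arm. Otherwise define a modified population explicitly and do not call it intention to treat.
- The withdrawal rule may stay as the primary analysis. Pair it with two pre-specified sensitivity analyses, unless the analysis plan already has them. The first is a worst case for SABR, in which withdrawals without documented progression count as not progressed on observation and as progressed on SABR. The second treats such withdrawals as missing.
- Report withdrawals by arm and reason.
- State that the 85% power assumes no scored withdrawals, and give the power at one or two plausible rates.

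The cost is a few sentences of protocol wording, a few extra analyses and a slightly less favourable power statement. If replaced patients are kept, the analysed total may exceed 54.

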##### 2.4.2.2.Analysis of secondary objectives

For safety analysis, adverse events will be summarized by type and grade.Hazard rate estimates and 95% confidence intervals as well as Kaplan-Meier (KM) estimates will be calculated for PFS, ADT-FS, TTLP and TTDP. The median PFS, ADT-FS, TTLP and TTDP will be reported.Each metastatic lesion will be considered a target lesion and independently evaluated for response using RECIST 1.1 or bone scan evaluation criteria below. The lesion will be coded as locally controlled if it is considered stable radiographic disease or if there is evidence of a partial or complete response. Local control assessment will start at three months following randomization and continuous assessment will be pursued during the follow-up period. The proportion of locally controlled lesions will be estimated using generalized estimating equations.QoL will be assessed using the Brief Pain Inventory form. An overall score will be calculated pre-treatment and at the time of the 2^nd^ radiologic reassessment. The change in score will be evaluated by paired t-test.

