**Fig. 1 Fig1:**
[figure not shown]
ORIOLE Study Schema. Subjects who meet eligibility criteria and qualify for enrollment will be stratified and randomized as demonstrated

The following is a detailed outline, after randomization, involving each study arm:Observation Arm: Active Clinical Surveillance
Defined with 3 time points, involving the following:

Day 1Standard blood tests [complete blood count with differential (CBC w/Diff), lactate dehydrogenase (LDH), serum chemistry, and PSA evaluation]Research laboratory tests: CAPP-Seq, rectal swab, and Color Test

Day 90Physician examination, medical history, medication review, performance status, quality of life (QoL) and adverse event (AE) evaluationsStandard blood tests (CBC w/Diff, LDH, serum chemistry, testosterone, and PSA evaluation)Research blood tests: CAPP-Seq

Day 180Physician examination, medical history, medication review, performance status, QoL and AE evaluationsStandard blood tests (CBC w/Diff, LDH, serum chemistry, testosterone and PSA evaluation),Research blood tests: CAPP-SeqImaging: bone scan and CT/MRI
2.SABR Arm:
Defined with 3 time points, involving the following:Day 1Standard blood tests (CBC w/Diff, LDH, serum chemistry, and PSA evaluation)Research laboratory tests: EPIC HD-CTC, ImmunoSEQ, CAPP-Seq, rectal swab, and Color TestImaging: ^18^F-DCFPyL PET/CT or PET/MRI
Day 90Physician examination, medical history, medication review, performance status, QoL and AE evaluationsStandard blood tests (CBC w/Diff, LDH, serum chemistry, testosterone, and PSA evaluation)Research blood tests: ImmunoSEQ, CAPP-Seq
Day 180Physician examination, medical history, medication review, performance status, QoL and AE evaluationsStandard blood tests (CBC w/Diff, LDH, serum chemistry, testosterone, and PSA evaluation)Research blood tests: EPIC HD-CTC, CAPP-SeqImaging: Bone scan and ^8^F-DCFPyL PET/CT or PET/MRI
Research Imaging
^18^F-DCFPyL PET/CT or PET/MRI images will be evaluated and compared to bone scan. However, additional sites(s) of suspected metastatic disease detected using ^18^F-DCFPyL will not be considered for treatment by SABR or undergo further evaluation. The results of PSMA-targeted PET imaging will not be made available to the treating physicians until after the trial is completed and these results will not be made available to the patient.SBRT/SABR Planning and Dosage:

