Site-specific grade 4/5 toxicity will be monitored in the SABR arm. If it becomes evident that the proportion of grade 4/5 toxicity at specific sites convincingly exceeds 20%, the study will be halted for a safety consultation. Specifically, we will apply a Bayesian toxicity monitoring rule that suspends the enrollment for a posterior probability ≥ 75% of toxicity being larger than 20%. The monitoring rule uses Beta (0.5, 5.5) as prior distribution, meaning our prior guess of the proportion of toxicity is 8.3% with a 90% chance that this proportion is 0.04%-30.6%.

Follow-Up:Patients will be followed from Day 1 to Day 180.All AEs and serious adverse events (SAEs) are recorded on source documents. The investigator will follow up on all AEs and SAEs until the events have subsided, returned to baseline or, in case of permanent impairment, until the condition stabilizes.

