#### Response criteria

Evaluation of Target Lesions and PSA Response

Complete Response (CR): Disappearance of all target lesions and PSA below baseline
Partial Response (PR): At least a 30% decrease in the sum of the longest diameter (LD) of target lesions, taking as reference the baseline sum OR at least 1/3 of lesions are stable or resolved by bone scan AND PSA below baseline
Progressive Disease (PD): At least a 20% increase in the sum of the LD of target lesions, taking as reference the smallest sum LD recorded since treatment initiation OR the appearance of >1 new lesion(s) by bone scan OR PSA ≥25% above nadir or > 50 ng/ml.
Stable Disease (SD): Neither sufficient shrinkage to qualify for PR nor sufficient increase to qualify for PD, taking as reference the smallest sum LD since treatment initiation OR PSA > baseline but not ≥25% above nadir and <50 ng/ml.
Complete Response (CR): Disappearance of all target lesions and PSA below baseline
Partial Response (PR): At least a 30% decrease in the sum of the longest diameter (LD) of target lesions, taking as reference the baseline sum OR at least 1/3 of lesions are stable or resolved by bone scan AND PSA below baseline
Progressive Disease (PD): At least a 20% increase in the sum of the LD of target lesions, taking as reference the smallest sum LD recorded since treatment initiation OR the appearance of >1 new lesion(s) by bone scan OR PSA ≥25% above nadir or > 50 ng/ml.
Stable Disease (SD): Neither sufficient shrinkage to qualify for PR nor sufficient increase to qualify for PD, taking as reference the smallest sum LD since treatment initiation OR PSA > baseline but not ≥25% above nadir and <50 ng/ml.

b.Evaluation of Best Overall Response: The best overall response is the best response recorded between treatment initiation and disease progression/recurrencec.Duration of Response: Response will be defined as evidence of CR, PR, or stable disease.

Duration of CR or PR: The duration of CR or PR will be recorded from the date criteria for CR or PR are first met until the first date current or progressive disease is objectively documented (taking as reference for progressive disease the smallest measurements recorded since treatment initiation).
Duration of Stable Disease: Stable disease will be recorded until the criteria for progression are met, taking as reference the smallest measurements recorded since the treatment started.

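### The listed schedule has post-baseline imaging only at Day 180, the end of follow-up, which conflicts with the planned time-to-event and response analyses of imaging outcomes

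*Protocol article*

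**What the plan says.** All places are in the protocol article.

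- **Evaluation of randomization and blinding:** "Patients will be re-evaluated for radiographic response 6 months after randomization".
- **Interventions, visit outline after Fig. 1:** Day 90 has examination, quality of life, adverse events and blood tests in both arms, and no imaging. Day 180 has bone scan with CT/MRI under observation, and bone scan with PSMA-targeted PET/CT or PET/MRI in the SABR arm. Of the PET, it says "The results of PSMA-targeted PET imaging will not be made available to the treating physicians until after the trial is completed".
- **Follow-Up:** "Patients will be followed from Day 1 to Day 180".
- **2.4.2.2 Analysis of secondary objectives:** hazard rates with 95% confidence intervals are planned, "Kaplan-Meier (KM) estimates will be calculated for PFS, ADT-FS, TTLP and TTDP", and "The median PFS, ADT-FS, TTLP and TTDP will be reported". The section adds: "Local control assessment will start at three months following randomization and continuous assessment will be pursued during the follow-up period". It also times the second pain score at a second radiologic reassessment.
- **Response criteria:** progressive disease by size is a 20% increase in the sum of longest diameters, "taking as reference the smallest sum LD recorded since treatment initiation". For response duration, "The duration of CR or PR will be recorded from the date criteria for CR or PR are first met".

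**The concern.** Locoregional and distant progression depend mainly on imaging. If the only scheduled scan falls on the last day of follow-up, it shows whether progression has occurred but says almost nothing about when. The planned curves, hazard rates and medians for TTLP and TTDP would then describe the visit calendar. Earlier event times could come only from unscheduled work-up, so any spread would partly show who happened to be scanned early, in a trial where treatment is not blinded.

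The Response criteria have a related problem. They use a size reference and a duration that presuppose more than one scan after treatment starts, and a treatment start that the observation arm does not have.

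**Working it through.** **1. The passages side by side.** The randomization section, the visit outline and the follow-up paragraph agree on one post-baseline imaging time point, Day 180, which is also the end of follow-up. Section 2.4.2.2 implies assessment from month 3 and at least two radiologic reassessments. No listed visit supplies the earlier one. The planning and cone-beam CT images in the SABR arm serve targeting, not response assessment.

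**2. The plan's own figure.** Sample size and accrual gives 85% power for 36 versus 18 patients, 40% versus 80%, one-sided Fisher's exact test at 0.05. Exact enumeration gives 0.8506, so it reproduces. The primary comparison needs only 6-month status and is not touched by this point.

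**3. What one scan does to time-to-event estimates.** The article gives no TTLP or TTDP rates. As stand-ins I use the composite progression rates by 6 months, p = 0.80 (observation) and p = 0.40 (SABR). I assume constant hazard and that every event is found at the month 6 scan.

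- Assumed true hazard, −ln(1 − p)/6: 1.609/6 = 0.268 and 0.511/6 = 0.085 per month.
- Assumed true median, ln 2 / hazard: 2.6 and 8.1 months.
- Events per person-month when all are dated at month 6, p/6: 0.80/6 = 0.133 and 0.40/6 = 0.067.
- Kaplan-Meier: the curve stays at 1.0 and drops once at month 6. The median is 6 months if at least half have an event, and otherwise not reached. Here it would be 6 months under observation and not reached under SABR.
- Assumed true hazard ratio: 0.085/0.268 = 0.317.
- Cox model with whole-patient counts of 14/36 and 14/18, all tied. With Breslow ties the score equation is 14 = 28 × 36θ/(36θ + 18), so 36θ + 18 = 72θ and θ = 0.50. That equals the risk ratio, (14/36)/(14/18) = 0.50. Efron ties, solved numerically, give 0.36.

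The same data thus yield 0.50 or 0.36 depending on how ties are handled.

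**4. Size reference for progressive disease.** Let S0 be the baseline sum and S180 the Day 180 sum. Read literally, the only sum recorded since treatment began is S180. The increase is then (S180 − S180)/S180 = 0, whatever the growth from baseline. If baseline counts, the reference is min(S0, S180), and the criterion is met when S180 ≥ 1.2 × S0. The same list names the baseline sum explicitly for partial response but not for progression.

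**5. Duration of CR or PR.** Both categories need an imaging finding. On the listed schedule they are first met at Day 180, when follow-up stops. The duration is censored at once and cannot be estimated.

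**The case against.** The strongest reply is that section 2.4.2.2 itself points to earlier or repeated imaging, and that the full protocol, which is not shown, may contain a month 3 scan. If so, most of the timing problem shrinks. This stands as a reason to ask for reconciliation rather than to assert that only one scan will be done. It does not remove the point, because the article's itemised visit list and its analysis section cannot both be followed.

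Several stronger readings are tempting, but the text does not support them.

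- **TTLP and TTDP have no event times.** They do have times, mostly tied at Day 180. The article does not define either endpoint, and it foresees progression at any time during the study, so unscheduled detection can date some events earlier.
- **All time-to-event analyses fail.** Under 2.4.2.1, progression also includes confirmed PSA rise, symptoms, start of ADT and death. PFS and ADT-FS can therefore have event dates before Day 180.
- **Response duration is always zero.** A CR or PR first seen at Day 180 has a censored duration, not an observed zero. Stable disease has its own duration rule and need not be zero.
- **Best overall response is just the Day 180 response.** Stable and progressive disease can be assigned on PSA, which is measured at Day 90. A patient may be stable then and progress by Day 180.
- **Size progression can never be detected.** That follows only if baseline is excluded. The primary definition cites RECIST 1.1 and sets no post-treatment reference, so the defect is one of wording.

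It is also fair to say that Kaplan-Meier handles censoring, while a simple proportion needs a rule for patients not scanned at Day 180. That cost is included in the fix.

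**Conclusion.** The point holds as an internal conflict, confined to secondary imaging outcomes. On the listed schedule, nearly all scan-detected locoregional and distant events fall at about Day 180. Medians are then limited to about 6 months or not reached, and hazard estimates follow the scan date.

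The figures above (hazard rates of 0.133 and 0.067 against 0.268 and 0.085 per month; hazard ratio 0.50 or 0.36 against 0.317) illustrate the mechanism. They do not estimate TTLP or TTDP. They rest on composite rates used as stand-ins, constant hazard, and no unscheduled detection. For the same reason, the article supports no estimate of the average dating delay in days.

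The size reference for progressive disease needs rewording, since read literally it leaves out baseline and has no meaning under observation. CR/PR duration is not estimable on this schedule. The primary Fisher comparison and its 85% power stand.

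**What to change.** 1. Reconcile the visit outline, the randomization section and the follow-up paragraph with section 2.4.2.2, so that one imaging schedule applies throughout, including the three-month start of local control assessment and the second radiologic reassessment.
2. If Day 180 is then the only scheduled scan, replace the Kaplan-Meier curves, hazard rates and medians for TTLP and TTDP. Report instead the proportion in each arm with locoregional and with distant progression by Day 180, with exact confidence intervals and the between-arm difference. State how withdrawals, deaths and patients not scanned at Day 180 are counted; the rule that withdrawal counts as progression is written for the primary objective. PFS and ADT-FS can stay as planned.
3. In the Response criteria, define the size reference for progressive disease in both arms as the smallest sum on study, including baseline.
4. On that same single-scan schedule, do not report duration of CR or PR.

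The cost is protocol and analysis wording. What is lost is a set of TTLP and TTDP curves that carry little timing information, and the proportions need an explicit rule for missing Day 180 scans.

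### Lesion-level local control is scored with patient-level response criteria that have no rule for a worsening existing bone lesion, and its assessment times do not match the scan schedule

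*Protocol article*

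**What the plan says.** Protocol article, section 2.4.2.2, sets the unit: "Each metastatic lesion will be considered a target lesion and independently evaluated for response using RECIST 1.1 or bone scan evaluation criteria below". The coding rule follows: a "lesion will be coded as locally controlled if it is considered stable radiographic disease or if there is evidence of a partial or complete" response. The estimator is also lesion-level: "The proportion of locally controlled lesions will be estimated using generalized estimating equations".

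The criteria that come below are in Response criteria, under a heading that joins target lesions with PSA. One limb of partial response (PR) reads "at least 1/3 of lesions are stable or resolved by bone scan AND PSA below baseline". Progressive disease (PD) is met by a 20% rise in summed diameters, by "the appearance of >1 new lesion(s) by bone scan OR PSA ≥25% above nadir", or by PSA above 50 ng/ml. The Methods/design paragraph of the abstract names RECIST 1.1 alone for local control.

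On timing, section 2.4.2.2 says: "Local control assessment will start at three months following randomization and continuous assessment will be pursued during the follow-up period". Evaluation of randomization and blinding says: "Patients will be re-evaluated for radiographic response 6 months after randomization". The abstract and Secondary endpoints place local control at 6 months after SABR.

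**The concern.** Local control is the direct measure of whether SABR ablates what it treats, and it is a named secondary endpoint. A coder told to judge each lesion is sent to definitions that need all lesions, their summed diameters, PSA and the count of new lesions. Two careful analysts could code the same scans differently. Depending on the reading, biochemical or distant failure could count against a treated lesion, or a true local failure could be recorded as control. The time points add a second doubt, because the plan describes assessments that its own visit list does not supply.

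**Working it through.** The plan gives no figure for local control, so there is none to reproduce. The steps below set the text side by side and show how far the coding can move.

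**1. Criteria against unit.**

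| Category | What Response criteria require | Usable for one lesion? |
|---|---|---|
| CR | Every target lesion gone, PSA under baseline | No |
| PR | 30% fall in summed diameters, or one third of lesions stable or resolved on bone scan, with PSA under baseline (unclear whether PSA governs both limbs) | Size limb only, if PSA does not attach to it |
| PD | 20% rise in summed diameters, or more than one new lesion on bone scan, or PSA | Size limb only |
| SD | Neither PR nor PD by size, or a PSA between baseline and the PD threshold | Size limb only |

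**2. Overlap.** A 30% shrinkage in a man whose PSA is 25% above nadir can be PR (if the PSA condition belongs only to the bone-scan limb) and PD at once. No order of precedence is given.

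**3. Reading A: lesions judged singly, imaging limbs only.** With one lesion, the one-third rule reduces to that lesion being stable or resolved, so it does no harm. The bone-scan PD limb counts new lesions only. An existing bone lesion that worsens on bone scan therefore meets no bone-scan PD limb and stays in SD, which is coded controlled. Let L be true per-lesion control and b the share of true local failures visible only as such worsening:

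coded = L + b(1 − L)

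The documents do not give b. With L = 75%, coded control runs from 75% (b = 0) to 75% + 25% = 100% (b = 1). With L = 90%, it runs from 90% to 100%. The error can only be upward.

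**4. Reading B: the criteria applied literally to the patient.** Examples with three lesions:
- One stable and two worse on bone scan, PSA under baseline: PR, so 3/3 coded against 1/3 true. If the two also raise summed diameters by 20%, PD is met as well and the result is undefined.
- Three stable, PSA 25% above nadir: PD, so 0/3 coded against 3/3 true.

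Let q be the share of patients with PSA or new-lesion PD, and m_k the share with k lesions (1 to 3, from Inclusion criteria). With at most three lesions, one stable lesion meets the one-third limb:

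coded = (1 − q) × Σ m_k k [1 − (1 − L)^k] / Σ m_k k

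Assumptions not in the documents: lesions are independent, 1, 2 and 3 lesions are equally common, PSA is below baseline whenever q is not triggered, and q takes the values shown. For L = 75% and q = 0: (0.75 + 1.875 + 2.953) / 6 = 93.0%.

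| True L | q = 0 | q = 0.1 | q = 0.2 | q = 0.4 |
|---|---|---|---|---|
| 75% | 93.0% | 83.7% | 74.4% | 55.8% |
| 90% | 98.0% | 88.2% | 78.4% | 58.8% |
| 95% | 99.1% | 89.2% | 79.3% | 59.4% |

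For L = 75%, the range from q = 0 to q = 0.4 is 98.4% to 59.1% if every patient has three lesions, and 75.0% to 45.0% if every patient has one.

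**5. Timing.** The visit list under Interventions has no Day 90 imaging in either arm, so nothing scheduled supports a three-month start. Follow-up runs from Day 1 to Day 180, and Secondary endpoints count Days 90 and 180 from randomization. SABR is given within three weeks of planning imaging. If SABR falls d days after Day 1, six months after SABR is about Day 180 + d, beyond follow-up for any d > 0. For illustration, with d = 21 the Day 180 scan comes 180 − 21 = 159 days after SABR.

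**6. Imaging at Day 180.** The observation arm has bone scan and CT/MRI. The SABR arm has bone scan and the investigational PET/CT or PET/MRI, with no separate CT/MRI listed. Whether lesion diameters will be measured from that scan is not stated.

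**7. Primary endpoint.** It has its own definition in section 2.4.2.1. Enumerating all tables for 18 and 36 patients at 80% and 40% with a one-sided Fisher test at 0.05 gives 85.06%, which reproduces the stated 85%.

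**The case against.** The best defence is that the text already implies an imaging-only, per-lesion reading. Lesions are judged independently, stable disease is qualified as radiographic, the abstract names RECIST 1.1 only, and the estimator presumes that lesions within a patient can differ. On that view the PSA limbs serve best overall response and duration of response. This stands as a possible reading, and it removes the one-third problem. It does not remove the gap for a worsening existing bone lesion, and the word radiographic qualifies stable disease but not the partial and complete responses in the same sentence. The size limb might catch a bone lesion whose diameter is measured, but section 2.4.2.1 applies the size rule to soft-tissue lesions.

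A reader might infer that the estimate is wrong in both directions. The documents do not show that: two-way error is a possible result of one reading, and its net sign depends on unknown quantities. A reader might also subtract the 40% progression rate from 1 and conclude that local control could read as low as 60%. That does not follow. The 40% belongs to the primary composite, which includes symptoms, ADT start, death and withdrawal, requires a confirmed PSA rise of at least 2 ng/mL, and counts one new bone lesion rather than more than one. Nor is 60% a bound, since step 4 gives lower values.

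On timing, the six-month re-evaluation is not said to be the only one, and the quality-of-life text mentions a second radiologic reassessment. The sample-size section also speaks of day 1 of SABR, which might suggest counting from treatment. These phrases deepen the conflict with the visit list and do not resolve it.

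An article may leave coding detail to the full protocol. Here, though, the article states the criteria and points to them, and they do not fit the endpoint.

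**Conclusion.** The concern holds as a stated rule that cannot be applied to its own endpoint. Depending on the reading, local control can be biased up or down, and the size and net sign cannot be determined from the documents. The figures in steps 3 and 4 are illustrations under stated assumptions, not estimates. The firmest error is upward, for bone lesions that worsen on bone scan, and it does not depend on the patient-level reading. The timing contradictions are on the page. The consequence is confined to a secondary endpoint. This should be corrected, but it does not threaten the trial's main comparison.

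**What to change.** For local control only, state per-lesion, imaging-only criteria. Each lesion is compared with its own reference measurement, and there is an explicit criterion for progression of an existing bone lesion at that site. Exclude the PSA, new-lesion and one-third-of-lesions limbs from this endpoint, and give an order of precedence where categories remain. Bring the abstract, section 2.4.2.2 and Response criteria into agreement.

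Reconcile the timing: the three-month start with the visit list, and six months after SABR with the six-month re-evaluation and Day 180 follow-up counted from randomization. Either side may be the intended one, and the authors must say which. Confirm that the SABR arm's Day 180 imaging supports the chosen measurement.

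The cost is wording and case-report coding. Whether further data are needed depends on that imaging check and on the time point chosen.
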